## Abstract

**Background:**

The functional significance of moderate riboflavin deficiency as it is currently assessed is not well understood. Animal and human studies have suggested a role for riboflavin in the absorption and mobilisation of iron and as such may be important in maintaining haematological status. Recent National Diet and Nutrition Surveys in the United Kingdom have shown that young women in particular are at risk of moderate riboflavin deficiency and low iron status.

**Methods/Design:**

A randomised placebo controlled intervention trial was conducted to investigate the effect of riboflavin supplementation on various measures of haematological status in a group of moderately riboflavin deficient young women aged 19 to 25 years. Women who were low milk consumers were initially screened for riboflavin status as assessed by the erythrocyte glutathione reductase activation coefficient assay (EGRAC). One hundred and twenty three women with EGRAC values >1.40 were randomised to receive 2 mg, 4 mg riboflavin or placebo for 8 weeks. In addition 36 of these women were randomly allocated to an iron bioavailability study to investigate the effect of the intervention on the absorption or utilisation of iron using an established red cell incorporation technique.

**Discussion:**

One hundred and nineteen women completed the intervention study, of whom 36 completed the bioavailability arm. Compliance was 96 ± 6% (mean ± SD). The most effective recruitment strategy for this gender and age group was e-communication (e-mail and website). The results of this study will clarify the functional significance of the current biochemical deficiency threshold for riboflavin status and will inform a re-evaluation of this biochemical threshold.

**Trial Registration:**

Current Controlled Trials Registration No. ISRCTN35811298

## Background

Although National Diet and Nutrition Surveys in the United Kingdom have reported a high prevalence of poor riboflavin status in certain sections of the population, in particular adolescent girls (15–18 years) [1] and young women (19–24 years) [2], the functional significance of marginal riboflavin deficiency is not well understood.

It has been reported that 95% of adolescent girls (15–18 yr) and 75% of young women (19–24 yr) in the UK have poor riboflavin status as measured by the erythrocyte glutathione reductase activation coefficient assay (EGRAC) [1,2]. The EGRAC assay is a well-established measure of riboflavin status and reflects the availability of the FAD cofactor for glutathione reductase in red blood cells. Although EGRAC is generally considered to be a functional measure of riboflavin status, the exact relationship between EGRAC values and any specific function has not been well established. Studies in animal models have highlighted adverse effects of riboflavin deficiency on various aspects of iron handling [3,4], but supporting evidence from human studies is limited. Randomised controlled trials carried out in riboflavin deficient [5,6] and moderately deficient [7] populations have suggested that riboflavin supplementation might have beneficial effects on measures of haematological status in these groups.

Although riboflavin deficiency is highly prevalent among young women in the UK, and poor iron status, expressed as low plasma ferritin, shows a moderate prevalence (30%) [2], it is not known whether there is any causal relationship and therefore whether improving riboflavin status will have any beneficial effect on measures of iron status.

### Study Aim

The overall aim of the study was to investigate the effect of a riboflavin supplement on a comprehensive range of haematological parameters and iron bioavailability in a group of young women with low riboflavin status.

### Objectives

The specific objectives of the study were as follows: -

• To recruit women with potentially low riboflavin status based on low milk consumption

• To screen recruited women for low riboflavin status

• To randomise women with low riboflavin status to an eight week placebo-controlled riboflavin intervention trial

• To measure the effect of the intervention on measures of riboflavin status, other B vitamin status and iron status

• To measure the effect of the intervention on iron bioavailability in a subgroup of the women

• To evaluate the diets of the women recruited to the study

## Methods/Design

The study design was a randomised, double-blind, placebo-controlled, intervention trial in which participants received one of two daily doses of riboflavin or placebo over a period of eight weeks and effects on measures of iron status and iron handling were evaluated. Ethical approval for the study was granted by the Sheffield University Research Ethics Committee (SMBRER15).

### Recruitment

Recruitment started in May 2006. The sample frame consisted of healthy women, aged 19–25 yr, living in the city of Sheffield, UK. The target was to recruit 200 women to the screening part of the study, as it was estimated that 66% of the sample would have low riboflavin status, judged as an EGRAC >1.40. In order to target women with a low riboflavin status, advertisements were sent out specifically asking for individuals who consumed less than 250 ml of milk per day since milk and milk products are the major contributors to riboflavin status in young women in the UK [2].

Recruitment strategies included approaching women from an existing volunteer database held at the Human Nutrition Unit at Sheffield University, a general e-mail campaign to students and staff at both the Sheffield Hallam University and the University of Sheffield, and the use of strategically-placed posters in the local area and advertisements in the local newspaper. Leaflets were also handed out to medical students at lectures. A website was developed to provide further information and allow prospective volunteers to choose a suitable time for their first visit to a number of screening clinics held at the unit. The information sheet was also available for downloading.

Volunteers were offered financial reimbursement for their time and effort according to the level of their involvement.

### Inclusion criteria

• Female

• Consumers of less than half a pint of milk (250 ml) a day

• Healthy

• Aged 19 – 25

### Exclusion criteria

• Regular blood donors (no donations 3 months before starting or during the study)

• Regular use of multivitamins or iron supplements

• Diagnosed gastrointestinal problems such as Inflammatory Bowel Disease or Coeliac disease

• Haematological disorders

• Haematochromatosis

• Pregnant or lactating

### Screening Clinic

The purpose of the screening clinic was four fold: -

1. to establish eligibility on the basis of the inclusion and exclusion criteria

2. to provide the volunteer with further information and gain informed consent for the whole study including the bioavailability arm

3. to collect the following demographic and health information by personal interview: -

• date of birth

• contact details

• GP address

• the use of medication

• supplement use

• the presence of known food allergies

• the existence of any medical conditions

• smoking status

• menstrual information – date of last period, length of cycle and contraceptive usage

4. to collect a 500 μl, non-fasted, finger prick sample for the measurement of riboflavin status (EGRAC) and plasma ferritin concentration.

Women with an EGRAC >1.40 were considered to be moderately riboflavin deficient and were invited to take part in the intervention study. Those women accepting the invitation were randomised to receive one of three supplements; 4 mg riboflavin, 2 mg riboflavin or placebo. The capsules were formulated by Research Products Limited (RPL, Blackpool) and were suitable for vegetarians and vegans (gelatin-free and coloured with chlorophyll). The researchers and participants were blinded to the identity of each capsule; only the suppliers of the capsules and an independent third party responsible for the randomisation knew the identity. The capsules, packed in pots of 60, were given at the first baseline visit and were sufficient for the entire intervention allowing 4 spare capsules for any losses. The riboflavin content in a random sample of each type of capsule was checked by high performance liquid chromatography.

### Randomisation to treatment

Randomisation was performed by an independent third party. Treatment codes were generated by ferritin stratification in blocks of 3 using a computer generated randomisation schedule. Three ranges of plasma ferritin were used for stratification; less than 15 ng/ml, 15.1–59.9 ng/ml and greater than 60 ng/ml. One in four women were allocated to the bioavailability arm by random sampling from those in the 4 mg and placebo groups of the intervention.

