### Additional Bioavailability Clinics

A sub-sample (one in four) of the women eligible for the main intervention study was chosen at random from the placebo and 4 mg groups to take part in the bioavailability study, in addition to taking part in the main study. Further information regarding this aspect of the study, including food diaries and food portion booklets, was sent to the women prior to attending the first clinic.

In particular they were advised not to eat red meat for 24 hours or drink alcohol for 12 hours prior to the first clinic. They were also advised not to take part in any vigorous exercise for the 24 hours before the clinic.

Women on the bioavailability arm were required to attend for extra clinics and extra procedures as described below (see fig. 1).

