#### Power calculation for the bioavailability

It was estimated that 15 subjects per group would be required to detect a 5% difference between the 4 mg and placebo intervention groups in iron incorporation into erythrocytes in response to intervention. This estimate was based on a mean bioavailabilty of 15% and a SD of 5% [9]with a power of 90% and a significance level of 0.05.

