### Initial Findings

#### Recruitment

Over a period of fifteen months, 256 women were screened for moderate riboflavin deficiency. From this initial screening, 145 were eligible for the intervention trial on the basis of an EGRAC>1.40. This represented 57% of our screened population. Of these 123 women agreed to take part in the main study (36 of these were randomly allocated to the bioavailability arm). In all, 4 women failed to complete the main study (none of whom, were in the bioavailability arm).

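### No ferritin restriction is stated for the bioavailability draw, so the 4 mg v placebo iron-incorporation model should adjust for ferritin and pre-intervention incorporation

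*Protocol article*

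**What the plan says.** For the main trial, the section Randomisation to treatment is specific. "Treatment codes were generated by ferritin stratification in blocks of 3 using a computer generated randomisation schedule", and "Three ranges of plasma ferritin were used for stratification", with cut-points near 15 and 60 ng/ml.

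For the bioavailability sub-study the same section says only that one woman in four was "allocated to the bioavailability arm by random sampling from those in the 4 mg and placebo groups". Additional Bioavailability Clinics repeats that the sub-sample "was chosen at random from the placebo and 4 mg groups to take part in the bioavailability study", and gives the one-in-four fraction with reference to the women eligible for the main study. Neither section mentions ferritin in connection with this draw.

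On size, Power calculation for the bioavailability states: "It was estimated that 15 subjects per group would be required". Under Initial Findings, Recruitment, the article reports that "36 of these were randomly allocated to the bioavailability arm" and that none of them failed to complete. The split of the 36 by arm or by ferritin range is not given.

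Each of these women has iron incorporation measured twice, once before the intervention and once at its end. The section Bioavailability data analysis names linear regression and ANOVA as the model class, with diagnostics. It names no baseline or ferritin term.

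**The concern.** The trial chose plasma ferritin as the one factor to balance at randomisation. The sub-study is the part whose endpoint is the handling of iron, and it is small, about 18 against 18. Stratified treatment codes balance ferritin over the full arms of about 41. They do not by themselves balance it in a sample of 18 taken from each arm. If no restriction was applied, one group can by chance hold more iron-depleted women than the other. Where ferritin is related to iron incorporation, that adds noise to the 4 mg v placebo difference. A model without a ferritin or baseline term leaves that noise in the estimate.

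**Working it through.** **Inputs.**
- 36 women drawn, from Initial Findings, Recruitment. An even split of 18 and 18 is assumed.
- 123 women in three arms, same section, so 41 per arm is assumed (123 / 3).
- Low-ferritin share of 30%, the Background's survey figure for young women. Using it as the share in the lowest stratum is an assumption; 20% to 40% is shown as a range. At 30%, 0.30 x 41 = 12.3, taken as 12 per arm.
- Stratification is taken to give both full arms the same number of low-ferritin women.
- Mean incorporation 15%, SD 5%, target difference 5 points, from Power calculation for the bioavailability.

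**The plan's own numbers first.** The planned main trial is 40 per arm, 120 in all. One in four of 120 is 30, which is 15 per group. One in four of the 145 eligible women is 36.25, and 36 were drawn. The fraction and the group size agree.

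**Ferritin imbalance if the draw was unrestricted within arms.** The number of low-ferritin women among 18 drawn from 41, of whom 12 are low, is hypergeometric:

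Var = 18 x (12/41) x (29/41) x (23/40) = 2.14 per group.

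SD of the difference between two groups = sqrt(2 x 2.14) = 2.07 women, or 2.07 / 18 = 0.115 as a share.

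With no stratification at all: sqrt(2 x 0.3 x 0.7 / 18) = 0.153.

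Summing the exact joint distribution of the two groups:

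| Low-ferritin women per arm of 41 | SD of difference in share | P(differ by 3 or more) | P(differ by 4 or more) |
|---|---|---|---|
| 8 (about 20%) | 0.100 | 0.16 | 0.05 |
| 12 (about 30%) | 0.115 | 0.22 | 0.09 |
| 16 (about 40%) | 0.123 | 0.26 | 0.11 |

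**What an imbalance could do to the estimate.** Three extra low-ferritin women in 18 is a difference in share of 3/18 = 0.167. The documents do not say how much more iron low-ferritin women incorporate. If the gap were 3 to 8 percentage points (an assumption), the shift in a post-intervention group difference would be 0.167 x 3 = 0.5 to 0.167 x 8 = 1.3 points. For scale, the standard error of that difference is 5 x sqrt(2/18) = 1.67 points and the target is 5 points. On the before-after response the shift is smaller, to the extent that a woman's ferritin-related level is the same on both occasions.

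**Arm split.** If the 36 were drawn from the two arms pooled (82 women) with no quota per arm, both groups reach 15 with probability 0.88. Power by the normal approximation is 85.1% at 18/18 and 83.3% at 14/22. For 30 women it is 78.2% at 15/15 and 75.2% at 11/19. An uneven split therefore costs about 2 to 3 points.

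**The case against.** The strongest reply is that an unrestricted draw is inferred from silence. Random sampling from two groups is also what one would write if a fixed number had been taken from each group, or from each stratum. A journal article commonly leaves such mechanics to the full protocol. This stands: the article does not show that the draw was unrestricted, only that no restriction is stated. The probabilities above are conditional on that.

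It is also fair to say that sampling at random within randomised arms introduces no bias, and that the standard error already reflects ordinary chance imbalance. That stands too. What is left is precision, and the protection of one small comparison against an unlucky draw. A further reply is that repeat measurement in each woman removes much of the ferritin effect. This is right, and it is why pre-intervention incorporation belongs in the model beside ferritin. The covariate list may be in an analysis plan not shown, in which case the fix may already be met.

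Three stronger readings are tempting, and the documents do not support them.
- A reader might infer that one in four contradicts 15 per group. It does not: Additional Bioavailability Clinics applies the fraction to women eligible for the main study, and a quarter of 120 is 30.
- A reader might infer 10 per group and 56% power by taking a quarter of the two sampled arms only. That denominator is not the one given there, and 36 women were drawn, not 20.
- A reader might infer that stratification gives the sub-study no protection. It gives part of it: 0.115 against 0.153.

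**Conclusion.** The point holds as a modest matter of precision. As described, the draw does not guarantee ferritin balance in the iron-incorporation comparison. If it was unrestricted, a gap of 3 or more low-ferritin women between groups has probability about 22% (16% to 26% for low-ferritin shares of 20% to 40%), and of 4 or more about 9% (5% to 11%). These figures assume 41 per arm, 18 drawn from each, and equal low-ferritin numbers in the full arms. The comparison is not biased, and a plausible shift in the estimate is below one standard error. The reason to act is that adjustment is nearly free and, with the Discussion reporting analysis still under way, still possible.

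**What to change.** In the linear model of Bioavailability data analysis that compares 4 mg with placebo, include two terms: ferritin stratum (or log baseline ferritin), and each woman's pre-intervention iron incorporation. Fix both terms before the treatment comparison is examined. Report the 36 women by arm and ferritin stratum, and say whether the draw was restricted by either.

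The ferritin term costs 1 degree of freedom as log ferritin, or 2 as three strata, and baseline incorporation costs 1. With 36 women and two groups, residual degrees of freedom fall from 34 to 32 or 31. No extra visit, sample or assay is needed. Quotas by stratum would have served the same end at the design stage, but the draw is complete.

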### Protocol for the intervention study

All eligible women were invited to take part in the intervention study (main study). As far as possible the dates for baseline blood collections were arranged to coincide with the middle of the menstrual cycle to reduce any effects of menstrual bleeding on measures of iron status. Once dates for all clinic visits had been agreed with the volunteer, an information pack containing a 4 day food diary, food portion booklet and a guide to the study was sent by mail.

Subjects attended the Clinical Research Facility at the Royal Hallamshire Hospital, Sheffield for all study clinics, which were held between 8.00 am and 10.00 am. Women were requested to fast from midnight the previous night.

Frequent contact was maintained by telephone or by email to remind the volunteers of clinic dates, the requirement for a fasted blood sample and the need to complete food diaries.

### Details of clinics

Women attended clinics according to whether they had been recruited to the intervention study alone or to the additional bioavailability study. The scheme for the clinic protocol is given in figure 1.

**Figure 1 F1:**
[figure not shown]
**Flow diagram for the RIBOFEM study**.

### Intervention study clinics

#### Baseline Clinic (Week 0)

This was an opportunity to explain the study in more detail and answer any questions. The height and weight of each subject were measured. The completed food diary was returned by the volunteer and the responses discussed with the researcher. The next food diary was given and dates agreed for completion prior to the next visit. A fasted blood samples was taken (15 ml, EDTA vacutainer) for baseline biochemistry and haematological measurements. Volunteers were given capsules with instructions for their use.

#### Interim clinic (Week 4)

A finger prick blood sample was taken (500 μl, EDTA microvette) for the measurement of EGRAC and ferritin, to allow the detection of early response to intervention and to check compliance. The second completed food diary was collected and discussed.

#### Post Intervention clinic (Week 8)

A fasted blood sample was collected (15 ml, EDTA vacutainer) for post intervention biochemistry and haematological measurements. Any remaining capsules were collected and counted.

#### Follow-up clinic (Week 12)

A further blood sample was taken (5 ml, EDTA vacutainer) for EGRAC and ferritin measurements to allow evaluation of the persistence of any response to intervention.

### Additional Bioavailability Clinics

A sub-sample (one in four) of the women eligible for the main intervention study was chosen at random from the placebo and 4 mg groups to take part in the bioavailability study, in addition to taking part in the main study. Further information regarding this aspect of the study, including food diaries and food portion booklets, was sent to the women prior to attending the first clinic.

In particular they were advised not to eat red meat for 24 hours or drink alcohol for 12 hours prior to the first clinic. They were also advised not to take part in any vigorous exercise for the 24 hours before the clinic.

Women on the bioavailability arm were required to attend for extra clinics and extra procedures as described below (see fig. 1).

#### Bioavailability: first pre-isotope clinic (2 weeks before the intervention study)

At this initial clinic, fasted volunteers attended the Clinical Research Facility (CRF) to receive the initial dose of the stable isotope labelled iron (^58^Fe = 95.1%). Prior to receiving this first dose, 5 ml blood were collected into a trace element free lithium heparin vacutainer and transferred into acid washed microcentrifuge tubes for background isotopic analysis. The labelled iron was given in two separate 2 mg doses, one with a specially prepared breakfast and the other with a specially prepared lunch. The isotope was prepared in aqueous solution (2 mg Fe as a ferrous sulphate solution per tube) by the Institute of Food Research (Norwich) and transported to Sheffield on dry ice. The aliquots of isotope were stored at -20°C until required. Just prior to administration each dose was diluted with a lemonade drink and given to the volunteer within 10 minutes of preparation. The drink containing the labelled iron was given with a simple breakfast of toast with jam and dairy-free spread, consumed at 0900 h. Four hours later the volunteers were given a lunch of pasta and instant tomato sauce, a plain bread roll and a second drink containing the 2 mg dose of labelled iron. Beverages and foods were carefully chosen so as not to contain any known enhancers or inhibitors of iron absorption. The beverage was free from phosphoric acid, tannin and vitamin C according to the manufacturers product description and the flavour and fizzy nature of the drink masked any taste of the iron. Additionally meals were chosen on the basis of a negligible iron or riboflavin content. The pasta sauce was selected on the basis of negligible vitamin C content and this was confirmed by enzymatic analysis using the method described by Vuilleumier [8], (< 1 mg/meal), using an automated centrifugal analyser (COBAS BIO Roche Products). Volunteers were allowed to leave the facility between meals but instructed not to eat, drink or exercise between the meals or for two hours after the lunch. Water was permitted ad libitum.

This clinic was also an opportunity to explain the study in more detail to the bioavailability volunteers, to answer any questions and to record the height and weight of each subject. The food diary was collected and the responses discussed with the researcher. The next food diary was given and dates agreed for completion prior to the next visit.

